### Preliminary studies

A prospective cohort study of all cases of KLA treated from 2005 to 2011 at two outpatient parenteral antibiotic therapy (OPAT) centers in Singapore (National University Hospital (NUH) and Tan Tock Seng Hospital (TTSH)) was completed to assess the safety and efficacy of OPAT for KLA [8]. One hundred and nine patients were enrolled. All patients had computed tomography (CT) or ultrasound (US) suggestive of a liver abscess, and either a positive blood culture or liver abscess fluid culture for *K. pneumoniae*. There were no deaths, or relapses post antibiotics. This study showed: mean duration of hospital stay of 15 days (range 2 to 84); mean duration of OPAT stay of 16 days (range 2 to 54); mean total time on IV antibiotics 31 days (range 11 to 98); and mean total oral antibiotics 6 weeks (range 0 to 21 weeks). Clinical response rate at four weeks was 73% and clinical cure one month after stopping antibiotics was 100% (using the same definitions as proposed in the section on endpoints below). Using discharge data from NUH over the same period, 196 patients met a diagnosis of KLA. This implies many patients did not reach OPAT, possibly due to logistical/financial reasons, but possibly also for medical reasons. Some would have remained inpatient at NUH, some would have been discharged to step-down care, and possibly some would have died. Clearly there is inherent selection bias in the above study because only patients well enough to be discharged to OPAT were included.

### Aims

Our study’s primary aim is to compare the efficacy of four weeks of IV antibiotics to early step-down to oral antibiotics in patients with KLA. Our results would help inform local and international practice guidelines regarding the optimal antibiotic management of KLA. A finding of non-inferiority in terms of clinical efficacy may translate to the wider adoption of a more cost-effective strategy that reduces hospital length of stay and improves patient-centered outcomes and satisfaction.

### Hypothesis

The hypothesis for our trial is that the degree of inferiority of our intervention (early step-down to oral antibiotics) to our active control (continued IV antibiotics) is no greater than 12%.

### Objectives

The primary objective is to compare the rate of clinical cure after four weeks of IV antibiotics to early step-down to oral antibiotics in patients with *Klebsiella pneumoniae* liver abscess, with clinical cure determined at Week 12 post randomization, and defined as CRP < 20 mg/l, plus absence of documented fever ≥ 38°C in the preceding seven days, plus most recent abdominal imaging showing that the maximal diameter of the abscess has reduced. The main secondary objective is to compare the rate of clinical response between the two study arms, with clinical response determined at Week 4 post-randomization, and defined as per clinical cure. Other secondary objectives are to compare the rate of the following during the study period, between the two study arms (assessed at 12 weeks): all cause mortality; unplanned readmission for any cause; unplanned need for drainage; metastatic complications; recrudescent or breakthrough *K. pneumoniae* bacteremia; need to escalate antibiotics due to worsening infection or secondary infection; vascular catheter complications. Additionally, to compare the length of hospital stay (from the date of randomization to the end of inpatient stay), length of time the subject requires medical leave following hospital discharge (censored at 12 weeks), total cost, subject quality of life (QoL), and adherence to study drug between the two study arms.

## Methods/design

### Study participants

The target number of subjects to be recruited is 152 over two years, across three academic teaching hospitals in Singapore (National University Hospital, Tan Tock Seng Hospital, and Singapore General Hospital). There is no restriction on subject recruitment by race or by gender. Pregnant and lactating women will be excluded from the study. Subjects will be identified by a research assistant (RA) who will be notified daily by radiology of all CT and US scans suggestive of liver abscess and by microbiology of all blood and fluid cultures positive for *K. pneumoniae*. The RA will screen eligible patients against study inclusion and exclusion criteria, and contact a study investigator to obtain informed consent. If the patient consents, the infectious diseases (ID) team will either take over management or co-manage the patient (with the primary physician’s agreement) to ensure that all elements of the protocol are adhered to. If the patient does not consent, the ID team will continue to provide consultation services.

### Inclusion criteria

1) Inpatient at time of enrollment.

2) Age ≥ 21 years.

3) CT or US scan within the preceding seven days suggestive of a liver abscess, as defined by presence of one or more focal areas of hypo- or hyper-attenuation within the liver.

4) *K. pneumoniae* isolated from abscess fluid or blood collected within the preceding seven days.

5) Able and willing to give informed consent.

### Exclusion criteria

Subjects meeting any of the following exclusion criteria at baseline will be excluded from participation:

1) Polymicrobial abscess - additional organisms isolated from blood or abscess fluid within the preceding seven days

2) 

a) *K. pneumoniae* resistant to ceftriaxone AND ertapenem

a) *K. pneumoniae* resistant to ciprofloxacin AND trimethoprim/sulfamethoxazole

3) On effective* IV antibiotics > seven days

4) 

a) Hypersensitivity to cephalosporins AND carbapenems; as defined by history of rash, urticaria, angiodema, bronchospasm or circulatory collapse following prior administration

a) Hypersensitivity to fluoroquinolones AND sulpha drugs; as defined by history of rash, urticaria, angiodema, bronchospasm or circulatory collapse following prior administration

a) History of penicillin anaphylaxis (angiodema, bronchospasm or circulatory collapse). Subjects with a history of only rash or urticaria or unknown reaction to penicillin can be included.

5) Inability to take oral medications for any reason

6) Severe sepsis or septic shock defined as unresolved hypotension (mean arterial pressure (MAP) < 70 mmHg) or tachycardia (heart rate (HR) > 110/min), or requirement of inotropic support or ventilation at time of eligibility. Should the subject’s hypotension or tachycardia subsequently resolve, and they cease to require inotropes and ventilation within seven days, they may be reconsidered for eligibility

7) Established endophthalmitis at time of screening (patients with visual symptoms should have ophthalmology review prior to enrollment)

8) Established central nervous system abscess at time of screening (patients with focal neurology should have cranial CT prior to enrollment)

9) Women who are pregnant or breastfeeding

10) Inability to obtain consent from subject

11) Patients on tizanidine or theophylline

12) Patients on concomitant drugs that can result in prolongation of the QT interval (for example, class IA or class III antiarrhythmics) or with risk factors for torsade de pointes (for example, known QT prolongation, uncorrected hypokalaemia)

13) Patients whose *K. pneumoniae* tests resistant to ciprofloxacin, and those with contraindications to ciprofloxacin will be tested for glucose-6-phosphate dehydrogenase (G6PD) deficiency, and excluded if deficient

14) Severely immunocompromized (for example, active leukemia or lymphoma, generalized malignancy, aplastic anemia, solid organ transplant, bone marrow transplant within two years of transplantation, or transplants of longer duration still on immunosuppressive drugs or with graft-versus-host disease, congenital immunodeficiency, current radiation therapy, HIV/AIDS with CD4 lymphocyte count < 200 and patients or on immunosuppressant medications)

15) Creatinine clearance < 15 ml/min

*defined as antibiotics to which the *K. pneumoniae* isolate in blood or abscess fluid is susceptible.

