### Study design

This study is a multi-center randomized open-label active comparator-controlled non-inferiority trial. Subjects fulfilling the inclusion/exclusion criteria are randomized to one of two arms: intervention arm; or active control arm, as shown in Figure 1. Participants randomized to the active control arm will receive IV ceftriaxone 2 grams daily (or ertapenem 1 gram daily if resistant) to complete a total of four weeks of IV antibiotics until the assessment at Week 4 post randomization. Patients can be discharged to OPAT at any point post randomization if clinically well, at the discretion of the treating physician/ID team. Patients discharged to step-down care will be followed up in OPAT clinic at the same weekly intervals as patients discharged to home. Patients will be assessed at Week 4 for clinical response. If they do not meet criteria for clinical response (as defined in the section on endpoints) then they will receive a further two weeks of oral ciprofloxacin 750 mg twice daily (or trimethoprim/sulfamethoxazole 5 mg/kg twice daily if resistant) and then re-reviewed (see below).

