**Figure 1 F1:**
[figure not shown]
Trial entry, randomization and treatment flow diagram.

Participants randomized to the intervention arm will be immediately converted to oral ciprofloxacin 750 mg twice daily (or trimethoprim/sulfamethoxazole 5 mg/kg twice daily if resistant). Oral antibiotics will be continued until the Week 4 assessment. Patients can be discharged home at any point post randomization if clinically well, at the discretion of the treating physician/ID team. Patients will be followed-up weekly in OPAT to ensure the same follow-up as patients in the control arm. Patients will be assessed at Week 4 for clinical response. If they do not meet criteria for clinical response (as defined in the section on endpoints) then they will receive a further two weeks of oral ciprofloxacin 750 mg twice daily (or trimethoprim/sulfamethoxazole 5 mg/kg twice daily if resistant) and then re-reviewed (see below).

Baseline as well as serial clinical and laboratory data will be collected as per the trial schedule. Patients will be monitored daily by their clinical team in the hospital until discharge, with weekly assessments by the study team, and weekly study assessments as outpatients after discharge until the Week 4 assessment. If participants do not meet criteria for clinical response at Week 4 there will be a further Week 6 appointment at the end of the two-week extension of oral antibiotics. Patients not satisfying the criteria for clinical response after Week 6 will receive two-weekly extensions of oral antibiotics and two weekly visits, until they meet criteria for response. All participants will be asked to return to a follow-up assessment at Week 12 (all follow-up assessments will have a window of +/- three days).

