### Randomization

After informed consent is signed, randomization into intervention or active control arms will be performed with a 1:1 allocation ratio. Balanced treatment assignments will be achieved using permuted block randomization, stratified by:

1) Abscess drainage (yes/no);

2) *K. pneumoniae* resistant to first-line agents (ceftriaxone or ciprofloxacin) (yes/no);

3) Study site.

The block length is determined by the study statistician and will not be made known to the clinical investigators or site personnel. All randomization will go through SCRI. Randomization will be done via direct web randomization. Authorized study center personnel will randomize the patient via a password protected internet website. The randomization system will then determine the treatment arm and provide the subject number to be used for the patient. The site monitor/clinical research associate (CRA) will be informed immediately in the event that the web randomization is not successful. Back-up randomization opaque envelopes (and related procedures) will also be prepared and provided to the site in case of internet failure.

Study arm allocation will not be blinded.

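### Exclusions 2 and 4 check resistance and hypersensitivity separately, so a rare eligible patient has no usable listed agent in an arm; the stated trigger for the alternative agent also conflicts with other sections

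*Protocol article*

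**What the plan says.** Each arm has two listed agents: ceftriaxone or ertapenem in the IV arm, ciprofloxacin or trimethoprim/sulfamethoxazole in the oral arm.

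- **Exclusion criteria, item 2 (resistance).** A patient is excluded if the isolate is "resistant to ceftriaxone AND ertapenem", or "resistant to ciprofloxacin AND trimethoprim/sulfamethoxazole".
- **Exclusion criteria, item 4 (hypersensitivity).** A patient is excluded for "Hypersensitivity to cephalosporins AND carbapenems", or for "Hypersensitivity to fluoroquinolones AND sulpha drugs". A history of penicillin anaphylaxis also excludes.
- **Study design (trigger for the alternative).** Control patients receive ceftriaxone, "or ertapenem 1 gram daily if resistant". Intervention patients are "immediately converted to oral ciprofloxacin 750 mg twice daily (or trimethoprim/sulfamethoxazole 5 mg/kg twice daily if resistant". Control patients who do not meet the response criteria at Week 4 receive the same oral agents under the same condition.
- **Exclusion criteria, item 13.** Besides patients with ciprofloxacin-resistant isolates, "those with contraindications to ciprofloxacin will be tested for glucose-6-phosphate dehydrogenase (G6PD) deficiency" and are excluded if deficient. Study visits and procedures and Table 1, footnote 10, repeat this testing rule.
- **Study intervention.** Both agents of each arm are listed as alternatives, with no condition for choosing between them.

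**The concern.** The paired conditions in items 2 and 4 appear designed to ensure that every randomized patient could take at least one agent in either arm. Because resistance and hypersensitivity are tested one at a time, they do not ensure it: one agent can be ruled out by resistance and the other by hypersensitivity without either criterion being met.

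The second problem is the trigger. A patient hypersensitive to one class only is eligible under item 4, which makes sense only if the other agent is available to that patient. Item 13 points the same way for ciprofloxacin contraindications. Study design nevertheless ties the alternative to resistance alone. At stake is whether the written rules can send an eligible patient to an agent that is inactive or to which a reaction is on record. The protocol states no figure on this point, so the check is one of logic, with a rough estimate of frequency.

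**Working it through.** **Step 1: patterns with no usable agent.** For one arm, each of the two agents may or may not be resisted (R1, R2) and may or may not belong to a class to which the patient is hypersensitive (H1, H2); 1 is first-line and 2 is the alternative. That gives 2 × 2 × 2 × 2 = 16 patterns. An agent is unusable if it is resisted, if the patient is hypersensitive to it, or both, which is 3 of its 4 states. Neither agent is usable in 3 × 3 = 9 patterns.

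**Step 2: what items 2 and 4 remove.** Resistance to both covers 4 patterns, hypersensitivity to both covers 4, and 1 is common to them: 4 + 4 − 1 = 7. All 7 are among the 9, so 9 − 7 = 2 no-usable-agent patterns stay eligible in each arm.

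**Step 3: the 16 − 7 = 9 eligible patterns, with the agent assigned by the literal trigger** (alternative if R1, otherwise first-line):

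| | No hypersensitivity | H1 only | H2 only |
|---|---|---|---|
| **No resistance** | first-line, usable | first-line, **patient reacts**; alternative usable | first-line, usable |
| **R1 only** | alternative, usable | alternative, usable | **no usable agent** |
| **R2 only** | first-line, usable | **no usable agent** | first-line, usable |

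Six of the nine work as written, two leave no usable agent, and in one the stated trigger names the agent the patient reacts to although the other is usable.

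The no-usable-agent patterns are:
- oral arm: ciprofloxacin-resistant isolate with sulpha hypersensitivity, or trimethoprim/sulfamethoxazole-resistant isolate with fluoroquinolone hypersensitivity;
- IV arm: ceftriaxone-resistant isolate with carbapenem hypersensitivity, or ertapenem-resistant isolate with cephalosporin hypersensitivity.

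**Step 4: does another rule close the gap?** Item 5 concerns inability to take oral medication. Item 13 removes only G6PD-deficient patients. The penicillin anaphylaxis rule concerns a different class. The Withdrawal criteria act only after entry. None closes it.

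**Step 5: frequency.** The protocol gives no hypersensitivity rate, so these rates are assumptions: 2% resistance per agent, 1% to 3% hypersensitivity per class, independent of each other. The target of 152 is from Study participants.

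- One cross pattern: 0.02 × 0.01 × 152 = 0.03 to 0.02 × 0.03 × 152 = 0.09 patients.
- All four cross patterns: 4 × 0.03 = 0.12 to 4 × 0.09 = 0.36 patients. With 1:1 allocation about half would be allocated to the affected arm. Doubling both upper rates gives 4 × 0.04 × 0.06 × 152 = 1.5.
- Hypersensitivity to one first-line class: 0.01 × 152 = 1.5 to 0.03 × 152 = 4.6 patients, about half of them allocated to that class.

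The Abstract describes the implicated strain as almost always ciprofloxacin-susceptible, and in the Taiwanese series in the Background all 160 monoinfection isolates resisted only ampicillin. The assumed 2% may therefore be too high.

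**The case against.** The strongest reply concerns the trigger. Study intervention lists both agents of each arm without condition. G6PD testing for ciprofloxacin contraindications appears in three places and makes sense only if the alternative oral agent is meant for those patients. Requiring hypersensitivity to both classes in item 4 carries the same implication. On this view the condition in Study design is an incomplete statement, not an instruction to give a drug despite a recorded reaction. That stands as a reading of intent, and a reader who infers that the protocol means to expose allergic patients goes too far. It does not remove the conflict: no section says that hypersensitivity or contraindication triggers the alternative, and the IV arm has no counterpart to the G6PD rule.

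Practice would also protect patients. The trial is open-label, the infectious diseases team manages or co-manages each patient, drug allergies are recorded at screening, and the investigator may withdraw a patient from treatment on safety grounds. This makes unknowing administration unlikely, but it works by departing from the written rule.

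A condensed article may leave drug selection to the full protocol. Here, however, the criteria and triggers are printed in detail, and the fault lies in what they state.

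Two further inferences are not supported. A reader might conclude that the arms become blurred and the non-inferiority comparison is weakened. But a patient hypersensitive to one class can stay in the allocated arm on its other listed agent, and patients with no usable agent number under one on the assumed rates. A reader might also object to the stratification factor, "resistant to first-line agents (ceftriaxone or ciprofloxacin) (yes/no", because it omits hypersensitivity. The Randomization section does not say that this factor is meant to balance use of the alternative agents, and resistance is a reasonable factor in its own right.

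**Conclusion.** The point holds as a minor matter of safety and consistency. The gap between items 2 and 4 is certain as logic: 2 of 16 patterns per arm are eligible with no usable listed agent. These are counts of patterns, not of patients; the expected number is under 1 of 152 on assumed rates of 2% resistance and up to 3% hypersensitivity. The conflict over the trigger is also on the page. It could concern about 2 to 5 enrolled patients per first-line class at an assumed 1% to 3%, roughly half of them allocated to that class. No effect of consequence on the primary analysis is shown, and the sample size is untouched. Nothing here requires replacing a test of resistance with a test of susceptibility, or redefining the stratification factor.

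**What to change.** 1. Reword items 2 and 4 (the paired conditions) as one joint check: for each arm, at least one listed agent must be ruled out by neither resistance of the isolate nor hypersensitivity of the patient. The 2 eligible no-usable-agent patterns per arm then fall to 0, and 7 patterns per arm remain eligible instead of 9.
2. Reconcile the trigger wording in Study design (both arms and the oral extension after Week 4) and in Study intervention with exclusions 4 and 13, the G6PD rule in Study visits and procedures, and Table 1, footnote 10. Which agent such a patient receives is for the sponsor to settle.

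The cost is a wording change and one eligibility check on the case report form. Antibiotic sensitivities and drug allergies are already collected at screening, so no test is added. The downside is that a very small number of patients become ineligible.

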### Withdrawal criteria

A patient may be withdrawn from the study at any point if he or she withdraws consent, or if the investigator deems it is in the best interest of the patient or due to safety concerns (adverse reactions due to study drug, better treatment option available, and so on). Any patient withdrawn from the study intervention would remain in follow-up for observation of safety and efficacy endpoints. However, all patients are free to withdraw completely from the study at any time, without giving a reason. Should they elect to leave the study then they will default to standard of care, which is IV ceftriaxone 2 g daily for four weeks followed by oral ciprofloxacin for two weeks. Patients already randomized to the oral treatment arm may elect to stay on oral antibiotics for the remainder of their allocated treatment duration. Subjects who drop out will not be replaced. Any patient withdrawn from the study intervention would remain in follow-up for observation of safety and efficacy endpoints. They would be asked to return for the Week 12 assessment. If they decline, then they will be followed as per institutional routine practice - usually two weeks after completion of antibiotics.

### Study design

This study is a multi-center randomized open-label active comparator-controlled non-inferiority trial. Subjects fulfilling the inclusion/exclusion criteria are randomized to one of two arms: intervention arm; or active control arm, as shown in Figure 1. Participants randomized to the active control arm will receive IV ceftriaxone 2 grams daily (or ertapenem 1 gram daily if resistant) to complete a total of four weeks of IV antibiotics until the assessment at Week 4 post randomization. Patients can be discharged to OPAT at any point post randomization if clinically well, at the discretion of the treating physician/ID team. Patients discharged to step-down care will be followed up in OPAT clinic at the same weekly intervals as patients discharged to home. Patients will be assessed at Week 4 for clinical response. If they do not meet criteria for clinical response (as defined in the section on endpoints) then they will receive a further two weeks of oral ciprofloxacin 750 mg twice daily (or trimethoprim/sulfamethoxazole 5 mg/kg twice daily if resistant) and then re-reviewed (see below).

**Figure 1 F1:**
[figure not shown]
Trial entry, randomization and treatment flow diagram.

Participants randomized to the intervention arm will be immediately converted to oral ciprofloxacin 750 mg twice daily (or trimethoprim/sulfamethoxazole 5 mg/kg twice daily if resistant). Oral antibiotics will be continued until the Week 4 assessment. Patients can be discharged home at any point post randomization if clinically well, at the discretion of the treating physician/ID team. Patients will be followed-up weekly in OPAT to ensure the same follow-up as patients in the control arm. Patients will be assessed at Week 4 for clinical response. If they do not meet criteria for clinical response (as defined in the section on endpoints) then they will receive a further two weeks of oral ciprofloxacin 750 mg twice daily (or trimethoprim/sulfamethoxazole 5 mg/kg twice daily if resistant) and then re-reviewed (see below).

Baseline as well as serial clinical and laboratory data will be collected as per the trial schedule. Patients will be monitored daily by their clinical team in the hospital until discharge, with weekly assessments by the study team, and weekly study assessments as outpatients after discharge until the Week 4 assessment. If participants do not meet criteria for clinical response at Week 4 there will be a further Week 6 appointment at the end of the two-week extension of oral antibiotics. Patients not satisfying the criteria for clinical response after Week 6 will receive two-weekly extensions of oral antibiotics and two weekly visits, until they meet criteria for response. All participants will be asked to return to a follow-up assessment at Week 12 (all follow-up assessments will have a window of +/- three days).

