**Assessments**	**Pre-enrolment (routine care)**	**Screening**	**Once between day 0 and day 7**	**Day 2–3, rpt every 2-3d until negative**	**Any point in study period if temp ≥38°C and any other secondary infection suspected**	**Daily**	**Every 7 days (+/- 3d)**	**Day 28 (+/- 3d)**	**Day 42 (+/- 3d) **** *(if oral continued)* **	**Day 56 (+/- 3d) **** *(if oral continued)* **	**Day 70 (+/- 3d) **** *(if oral continued)* **	**Day 84 (+/- 7d)**
Informed consent		X										
Randomisation		X										
Demographics		X										
Past medical history^1^		X										
Antibiotic history		X^2^					X^3^	X^3^	X^3^	X^3^	X^3^	X^3^
Symptom assessment^4^		X					X	X	X	X	X	X
Temperature		X				X^5^	X^6^	X	X	X	X	X
Physical examination^7^		X					X	X	X	X	X	X
Screen metastatic complications^8^		X					X	X	X	X	X	X
Adverse event monitoring							X	X	X	X	X	X
Adherence check							X	X	X	X	X	X
Ophthalmology assessment			X									
FBC		X^9^					X	X	X	X	X	X
RP1		X^9^					X	X	X	X	X	X
LFT		X^9^					X	X	X	X	X	X
CRP		X^9^					X	X	X	X	X	X
Procalcitonin		X^9^					X	X	X	X	X	X
Urine pregnancy test		X^9^										
G6PD		X^10^										
Blood cultures	+/-	X^11^		X	X							
Chest X-ray		X^11^										
Abdominal CT or US	X^12^							X^13^		X^14^		X^15^
Abscess drainage^16^	+/-											
Abscess fluid culture^16^	+/-											
Study drug						X						
Subject diary of healthcare expenses						X						
Quality of Life Survey		X						X				X

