^1^Full medical history including comorbidities, current medications, drug allergies, presenting and current symptoms. ^2^Document all antibiotics taken during this treatment episode up until enrollment. ^3^Include study drug and any additional antibiotics given. ^4^Standardized checklist. ^5^Self recorded daily temperature recording at home post discharge until Day 28 or until meeting criteria for clinical response. ^6^Self recorded weekly temperature recording at home after meeting criteria for clinical response, with weekly reminder call from the study team. ^7^Measurement of blood pressure, heart rate, and cardiovascular, respiratory and abdominal examination. ^8^Screen consists of standardized checklist of symptoms and signs, which if present trigger relevant investigations. ^9^If not already done in previous 48 hours. ^10^Only in patients whose *K. pneumoniae* tests resistant to ciprofloxacin, and those with contraindications to ciprofloxacin. ^11^If not already done in previous seven days. ^12^Scans must be within the preceding seven days. ^13^Day 28 scan to be performed within three days prior to the Day 28 visit. ^14^Day 56 scan to be performed within three days prior to the Day 56 visit, only in those patients failing to meet criteria for clinical response at day 42. ^15^Day 84 scan to be performed within three days prior to the Day 84 visit, only in those patients failing to meet criteria for clinical response at day 70. ^16^At any point during the current treatment episode.

Patients will be reviewed every seven days whilst inpatient. Assessment will consist of a standardized clinical assessment consisting of temperature, blood pressure, heart rate, symptom assessment and clinical examination. Blood tests (FBC, RP1, LFT, CRP, procalcitonin) will be performed a minimum of once every seven days while in hospital. In addition, temperature will be measured daily for all participants until Day 28 or meeting criteria for clinical response, whichever is longest. While inpatient or in OPAT this is part of routine clinical care; and for patients on the intervention arm (oral antibiotics), patients will be given thermometers to use daily after hospital discharge. Repeat blood cultures will be performed at day two to three post randomization on all patients with a positive blood culture at/prior to enrollment. If this remains positive it will be repeated every two to three days until negative. This is to ensure clearance of bacteremia.

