The analysis of safety endpoints will be on the as treated population. Numbers and percentages needing to stop study drug due to toxicity will be summarized between the two treatment arms; as will the numbers and percentages of reported clinical symptoms of moderate/severe grade (by body systems). Numbers and percentages of patients with at least one adverse event up to 12 weeks post randomization or 30 days post last study treatment (whichever is last) will be tabulated by treatment group and details of the event will be summarized. The numbers and percentages of serious adverse events will be tabulated by treatment group and the details will be summarized. Numbers needing to escalate antibiotics due to worsening infection or secondary infection at any point between randomization and Week 12 will be compared between arms using the Fisher’s exact test and the Clopper and Pearson CI will be calculated.

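### After Week 4, scheduled adverse-event, laboratory and metastatic checks depend on Week 4 response, so ascertainment in the 12-week comparisons can differ by arm, probably slightly

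*Protocol article*

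**What the plan says.** The Study design section has outpatients seen by the study team weekly, in its words "weekly study assessments as outpatients after discharge until the Week 4 assessment". After that, visits follow response: "If participants do not meet criteria for clinical response at Week 4 there will be a further Week 6 appointment", and those still short of the criteria after Week 6 "will receive two-weekly extensions of oral antibiotics and two weekly visits, until they meet criteria for response". For everyone, "All participants will be asked to return to a follow-up assessment at Week 12".

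Table 1 (trial schedule) matches this. Its Day 42, 56 and 70 columns are each headed "if oral continued". They are marked for the row "Adverse event monitoring", for full blood count, renal panel, liver tests, CRP and procalcitonin, and for the metastatic screen.

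For patients who have responded, Table 1 footnote 6 provides: "Self recorded weekly temperature recording at home after meeting criteria for clinical response, with weekly reminder call from the study team". The article gives this call no other purpose.

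The comparisons nevertheless run to Week 12. Statistical analysis tabulates by arm "Numbers and percentages of patients with at least one adverse event up to 12 weeks post randomization" (or to 30 days after the last study treatment, if later). Study endpoints lists metastatic complications up to Week 12 as a secondary endpoint.

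**The concern.** Up to Day 28 both arms have the same weekly assessments. From Day 28 to Day 84 the number of scheduled checks depends on whether the patient met the response criteria at Week 4. That is the trial's main secondary endpoint, it occurs after randomization, and it may differ between oral and IV treatment. If it does, one arm is examined more often than the other in those eight weeks. Events found mainly because someone looks or asks would then be recorded unequally: abnormal laboratory values, mild or short-lived symptoms, and early symptoms that trigger a search for metastatic infection.

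The protocol cares about this kind of imbalance. Its Background section criticises the earlier randomized trial because the oral arm was reviewed less often than the control arm, and Study design gives the oral arm weekly clinic review so that follow-up matches. As Study design is written, that safeguard stops at Week 4, in an open-label trial.

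**Working it through.** **Inputs from the article.** Weekly visits to Day 28; interim visits at Days 42, 56 and 70 for non-responders only; a common visit at Day 84; Week 4 response of 73% in the prior cohort (Preliminary studies); 152 patients at 1:1, so 152/2 = 76 per arm. The article gives no figure for the effect examined here.

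**Assumptions, not in the article.** Oral-arm Week 4 response of 61%, which is 12 points below 73%; the capture and event rates stated below.

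**1. Length of the gap.** 84 - 28 = 56 days. With the ±3-day window in Study design it is 50 to 62 days. With Table 1's ±7 days at Day 84 it is 46 to 66 days.

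**2. Who is affected.** At 73% response, 76 × 0.73 ≈ 55 patients per arm have one scheduled visit after Day 28. The other 76 × 0.27 ≈ 21 have two to four.

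**3. Difference in visits.** Interim visits per patient = (1 - response) × k, with k = 1 to 3 visits per non-responder.
- At 73%: 0.27 × k = 0.27 to 0.81.
- At 61%: 0.39 × k = 0.39 to 1.17.
- Adding the Day 84 visit: 1.27 to 1.81 against 1.39 to 2.17, a difference of 0.12 to 0.36 visits per patient.

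**4. Effect on recorded events, relative.** Suppose the true event rate is the same in all patients and events are spread evenly over 84 days. Events in the 14 days before a scheduled visit are all recorded; other events after Day 28 are recorded with probability q. Let c be the share of Days 28-84 that lies within 14 days before a visit.
- Responder: 14/56 = 0.25.
- Non-responder continuing to Day 84: 1.
- Non-responder who responds at Day 42: (14 + 14)/56 = 0.50.

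Recorded share for Days 28-84 = c + (1 - c)q. Over 12 weeks, with Days 0-28 fully recorded, it is 1/3 + (2/3)[c + (1 - c)q].

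| Non-responders continue to | c at 73% | c at 61% | Ratio Days 28-84, q = 0.3 / 0.7 | Ratio over 12 weeks, q = 0.3 / 0.7 |
|---|---|---|---|---|
| Day 84 | 0.4525 | 0.5425 | 1.102 / 1.032 | 1.056 / 1.020 |
| Day 42 | 0.3175 | 0.3475 | 1.040 / 1.011 | 1.021 / 1.007 |

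First row, q = 0.3: 0.4525 + 0.5475 × 0.3 = 0.6168 and 0.5425 + 0.4575 × 0.3 = 0.6798, ratio 1.102. Over 12 weeks the shares are 0.7445 and 0.7865, ratio 1.056. The 12-week excess is therefore about 0.7% to 5.6%.

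**5. Effect in percentage points.** Let t be the true Day 29-84 event rate, s the share recovered without interim visits (full recovery with them), and ΔR the response gap. The shift is t × (1 - s) × ΔR.
- t = 30%, s = 0.5: 0.30 × 0.5 × 0.12 = 1.8 points, or 0.018 × 76 ≈ 1.4 patients.
- s = 0.8, t = 10% to 30%: 0.2 to 0.7 points.
- s = 1 or ΔR = 0: zero.

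**6. The schedule is written in more than one way.**
- Study design ends weekly visits at Week 4. Table 1's seven-day column has no end date; it carries adverse events, bloods and the metastatic screen, and it holds footnote 6, which applies after response.
- Study visits and procedures states weekly clinic review after discharge in both arms without an end date, then describes Week 6 and later visits only for non-responders.
- The same section lists full blood count, CRP and procalcitonin at Week 12, whereas Table 1 also marks renal panel and liver tests at Day 84. On the text version a Week 4 responder has no scheduled renal or liver tests after Day 28.

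**The case against.** A reader might infer that the safety comparison is biased by design, or confounded with efficacy. The documents do not support that. The visit rule is the same in both arms, and every patient is seen at Day 84. A bias needs both a between-arm difference in Week 4 response and events that are not recovered at Day 84. Either arm could have the better response, so the direction is unknown too. The 12-point gap is borrowed from the non-inferiority margin for Week 12 cure, and the capture rates are assumed.

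A reader might also infer that responders have no contact for 56 days. They have a weekly call. What it asks may be set out in the full protocol, so a missing call script is not held against the article. The undated seven-day column and weekly clinic review also allow a reading in which checks continue throughout. That weakens any claim of a certain gap, but it leaves sites with two schedules to choose from.

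Three further points stand. Deaths, readmissions and serious adverse events come to light largely without scheduled visits. Metastatic complications are a secondary rather than a safety endpoint, and their work-up is triggered by symptoms and signs. Non-responders are still taking antibiotics, so closer monitoring of them is defensible, and part of any excess would be real toxicity of longer treatment rather than detection.

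What survives is narrower: on the Study design text, how closely patients are checked after Day 28 depends on a post-randomization outcome.

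**Conclusion.** The point holds as a conditional weakness in ascertainment. On the Study design text and the conditional visit columns of Table 1, Week 4 responders have a 56-day interval without a scheduled visit, while the article compares adverse events and metastatic complications by arm to Week 12. The likely size is small: about 1-6% relative over 12 weeks, or 0 to 1.8 percentage points, under the assumed 12-point response gap and the capture and event rates shown. It vanishes if response is equal or recall at Day 84 is complete. It concerns laboratory toxicity, mild or transient events and symptom-triggered metastatic findings. The sample size is unaffected. The case for acting is that the remedy is cheap; no material distortion has been shown. The conflicting schedule statements need reconciling whatever the size of the effect.

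**What to change.** - At the reminder calls falling at about Days 42, 56 and 70, ask every patient who has already responded the same standardized adverse-event and metastatic-symptom checklist that non-responders get at their visits. All patients in both arms then have symptom-based ascertainment on common days. Signs and laboratory values cannot be collected by telephone, so some difference remains.
- Keep the 12-week safety table as specified. Add a Day 0-28 table, where the schedules are identical, as a supplement and not a replacement: a table confined to Day 28 would miss toxicity from extended treatment.
- Keep the Day 42-70 laboratory results, labelled as collected only in patients still on antibiotics.
- Reconcile Study design, Study visits and procedures, and Table 1 with its footnotes on when the seven-day column ends and whether renal panel and liver tests are done at Week 12.

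The cost is slightly longer calls that are already planned, a short case report form page and one extra table. The downside is that more minor events will be recorded in responders. No treatment rule changes.
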